#### 3.2.1. Heart Rate Variability (HRV)

A Zephyr™ BioHarness™ BT (Zephyr Technology, Annapolis, MD, USA) will record HRV parameters. The Zephyr™ BioHarness™ BT is a heart rate transmitter belt simply positioned on the chest, with a 26 h recording time, a beat per minute within a 25–240 range, and respiratory rate within a 3–70 range. The aim will be to demonstrate that is it possible to detect anxiety using this easy to use and cheap device. Anxiety could also be detect using the respiratory rate. In addition, the Zephyr™ BioHarness™ BT will also measure the trunk’s movements with a 3-Axis accelerometer. Recommendations of the European Society of Cardiology and the North American Society (Task Force) will be followed to examine the HRV data. Time and frequency domains will be used to explore HRV. [50]. We will also apply the methodology developed by our team [51].

We will visually check the premature beats who will be automatically reject. Several element will be analyzed in time domain: R–R intervals and their standard deviation, the number of adjacent N–N differing by more than 50 ms divided by the total number of N–N inter-vals (pNN50) and the square root of the mean squared difference of successive R–R intervals (rMSSD). The pNN5 and rMSSD are related with high frequency (HF) power and therefore to parasympathetic activity. High (0.15–0.4 Hz) and low (0.04–0.15 Hz) frequency power will be examine in the spectral domain. HF is the principal efferent parasympathetic (vagal) activity to the sinus mode, LF is an indicator for both parasympathetic and sympathetic functions. The variations of thermoregulatory mechanisms, activity of the renin–angiotensin system and the function of peripheral chemoreceptors are partially reflects by very low frequency (VLF, 0.003–0.04 Hz). Normalized units (nu), corresponding to the relative value of each power component in proportion to the total power minus the VLF component, will also be used to assessed LF and HF. Thus, the best sympathetic and parasympathetic activity seems to be represented by LFnu and HFnu, respectively. The LF/HF ratio, that is, the sympathovagal balance, will also be calculated (Table 2) [52].

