#### 2.2.1. The Intervention: Neurolinguistic Programming and Sophrology

Each participant will benefit from an NLP and sophrology intervention. The sophrology/NPL program will be provided by a qualified sophrologist outside from the hospital and that will be specifically employed by Clermont-Ferrand University Hospital for the purpose of this study, in order to avoid any previous relation between volunteers and the therapist. NLP and sophrology will take place within the University Hospital of Clermont-Ferrand. A total of 6 to 8 sessions will be proposed for each participant, by group of up to fifteen participants. Two sophrology sessions will be offered per week at two different times for easier accessibility. Each session will last one hour. They can take place in a seated or standing position, without physical contact. The sessions will consist of breathing exercises, visualization, and dynamic relaxation as well as concentration exercises. Breathing exercises have two objectives: (1) to manage the stress using deep inspiration and short expiration; (2) to dynamize the body using pauses between inspiration and expiration. During visualization process, we will ask participants to think of something or someone reminding pleasure and sensation of fullness. Dynamic relaxation includes exercises mobilizing parts of the body in order to take consciousness of all body segments. Breathing exercises, visualization, and dynamic relaxation are tools that should lead to an improvement of the dimensions of concentration (physical, mental, and emotional). All exercises will be guided by sophrologist. The sophrology/NLP program is standardized. Each session will take place in a typical way: (i) dialogue between the sophrologist and the participants, which makes it possible to specify the objective(s) of the session as the sophrologist will ask more specific questions to adapt the content of the sophrology session that they propose if they think it will be useful; (ii) presentation of the conduct of the session (possible variations) and instructions promoting autonomy; (iii) this practice is guided by the sophrologist, with the goal being to help free individuals from tensions, to play down a situation that worries and finally to realize that we can deal with. Sophrology exercises are adapted to the difficulties encountered by the participants; and (iv) time for free expression after the practice to promote the integration of the technique while giving elements to the sophrologist to guide the rest of the sessions.

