**Frequency-domain**			
TP	Total power, i.e., power of all spectral bands	ms^2^	Overall autonomic activity
LF	Power of the low-frequency band (0.04–0.15 Hz)	ms^2^ (absolute power) or nu (relative power in normalized unit)	Index of both sympathetic and parasympathetic activity, with a predominance of sympathetic
HF	Power of the high-frequency band (0.15–0.40 Hz)		Represents the most efferent vagal (parasympathetic) activity to the sinus node
LF/HF	LF/HF ratio	-	Sympathovagal balance
VLF	Very low frequency (0.003–0.04 Hz)	ms²	Sympathovagal balance

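### Section 3.2.1 reads LFnu, HFnu and LF/HF as sympathetic and vagal indices without regard to breathing rate; below 9 breaths/min that reading fails, and this intervention trains breathing.

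*Protocol article*

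**What the plan says.** Section 3.2.1 of the protocol article sets the bands: "High (0.15–0.4 Hz) and low (0.04–0.15 Hz) frequency power will be examine in the spectral domain". It defines normalised units as "the relative value of each power component in proportion to the total power minus the VLF component" and draws the conclusion "Thus, the best sympathetic and parasympathetic activity seems to be represented by LFnu and HFnu, respectively". On the ratio it states: "The LF/HF ratio, that is, the sympathovagal balance, will also be calculated". Table 2 says of HF: "Represents the most efferent vagal (parasympathetic) activity to the sinus node". Raw LF is treated more cautiously in section 3.2.1: "LF is an indicator for both parasympathetic and sympathetic functions". Table 2 likewise calls LF mixed, though mainly sympathetic.

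Section 2.2.1 describes the intervention: "The sessions will consist of breathing exercises, visualization, and dynamic relaxation as well as concentration exercises". Section 2.6 and Table 1 place the recordings of the intervention period weekly, one in each session, with monthly recordings at other times. Under section 2.2, the intervention arm has its sessions between M1 and M3 and the deferred arm has none until after M3.

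The chest belt covers "a beat per minute within a 25–240 range, and respiratory rate within a 3–70 range". The only use that section 3.2.1 gives for the respiratory rate is the possible detection of anxiety. It is not among the example covariates for the mixed model in section 3.3.1.

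**The concern.** The vagal reading of HF power assumes that breathing lies inside the HF band. Respiratory modulation of heart rate appears at the breathing frequency. If a participant breathes below the lower limit of the band, that modulation is counted as LF power. On the rule in section 3.2.1, the recording would then show vagal loss and sympathetic gain when only the breathing rate has changed.

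In most trials this would be noise common to both arms. Here the treatment works partly through breathing, and over the period of the primary contrast only one arm is treated and recorded in sessions. Any misreading would therefore fall mainly on the intervention arm and run against the stated aim of showing improved heart rate variability. The belt already records what is needed to detect it.

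**Working it through.** **The plan's own figure.** Section 3.1 gives 85 per group for an effect size of 0.5, two-sided 5% and 90% power. n = 2 × (1.960 + 1.282)² / 0.5² = 84.1, rounded up to 85. With the t distribution, 85 per group gives power 0.900. Allowing for 15% loss, 85 / 0.85 = 100. The sample size reproduces and is not in dispute.

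**Band limits as breathing rates** (Hz × 60): 0.04 Hz = 2.4/min, 0.15 Hz = 9/min, 0.40 Hz = 24/min. Breathing at 9 to 24/min puts respiratory power in HF; breathing at 2.4 to 9/min puts it in LF. That respiratory power follows the breathing frequency is general physiology, taken here as an assumption.

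**Effect on the indices.** LFnu = 100 × LF / (LF + HF). Assume LF and HF are equal at 500 ms² and move a share s of HF power into LF, total unchanged:
- s = 25%: LF 625, HF 375, LFnu 62.5, LF/HF 1.67
- s = 50%: LF 750, HF 250, LFnu 75, LF/HF 3.0
- s = 75%: LF 875, HF 125, LFnu 87.5, LF/HF 7.0

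From a 70:30 split, s = 50% takes LFnu from 70 to 85; from 30:70, it takes LFnu from 30 to 65.

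**Simulation.** Five-minute series with constant respiratory amplitude (30 ms), a constant 0.09 Hz component (20 ms) and small noise; only the breathing rate varies. All amplitudes are assumed.

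| Breaths/min | LF (ms²) | HF (ms²) | LFnu | LF/HF | rMSSD (ms) | SDNN (ms) |
|---|---|---|---|---|---|---|
| 15 | 201 | 451 | 30.8 | 0.45 | 27.4 | 25.6 |
| 10 | 202 | 453 | 30.8 | 0.45 | 20.2 | 25.7 |
| 9.5 | 233 | 422.5 | 35.5 | 0.55 | 19.4 | 25.7 |
| 8.5 | 651 | 4.1 | 99.4 | 161 | 18.0 | 25.8 |
| 6 | 652 | 3.2 | 99.5 | 208 | 14.3 | 25.8 |

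The spectral indices jump at 9/min while SDNN stays level. rMSSD also falls as breathing slows, so it is not a fully independent check. Breathing varies more in real recordings than here, so the real step would be softer.

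**What a group difference could look like.** The documents give neither the share of recordings below 9/min nor an SD for HFnu, so this is illustration only. Take an SD of 20 points and a loss of 50 points per affected participant (the equal split, full move). With share p affected in the treated arm, the mean shift is 50p points and the treated-arm variance is 20² + p(1 − p) × 50². The pooled SD averages this with the control variance of 400:
- p = 0: no shift
- p = 10%: −5 points; variance 625; pooled SD √512.5 = 22.6; −0.22 SD
- p = 20%: −10 points; variance 800; pooled SD √600 = 24.5; −0.41 SD
- p = 30%: −15 points; variance 925; pooled SD √662.5 = 25.7; −0.58 SD

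**The case against.** **The documents give no breathing rate.** Section 2.2.1 describes deep in-breaths with short out-breaths, and pauses within the breathing cycle. It does not say that slow breathing is taught. Slowing from 16 to 11/min leaves the power in HF and does no harm. This stands: the share of affected recordings is unknown, above all for monthly recordings outside sessions.

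**The bands are not an error.** Section 3.2.1 says that published Task Force recommendations will be followed, and it cites a method of the team's own that is not shown. Details of signal processing may properly sit in a fuller document. This also stands, but the point does not rest on silence. The article states an interpretation, softened by the word seems but with no condition on breathing.

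**The misreading is limited in scope.** Raw LF is already called mixed, and SDNN, rMSSD and pNN50 are also planned. This stands: only LFnu, HFnu and LF/HF are clearly affected.

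**A reader might infer that the artefact could cancel the assumed effect of 0.5 or reverse the primary result.** The documents do not support that. Section 2.6 names no primary parameter, section 3.1 applies 0.5 to such parameters in general, and any offset depends on an assumed share and SD.

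**A reader might also infer that the HF band should be re-centred wherever breathing is slow.** That would make the outcome definition depend on a post-randomisation variable likely to differ by arm. It would also count non-respiratory LF power as vagal. Take 500 ms² of respiratory power at 6/min (0.10 Hz) and 500 ms² of other LF power spread evenly over 0.06 to 0.12 Hz. A band of ±0.015 Hz captures half of the latter (HF = 750 ms²), and ±0.05 Hz captures all of it (HF = 1000 ms²), with vagal activity unchanged.

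**Conclusion.** The concern holds in limited form. The stated reading of LFnu, HFnu and LF/HF is wrong for any recording with breathing below 9/min, and the design makes such recordings more likely in the intervention arm between M1 and M3. Within an affected recording the distortion can be near total: LFnu went from about 31 to above 99 in the simulation. Its size at group level cannot be derived from the documents. The illustrative −0.22 to −0.58 SD for shares of 10% to 30% rests on an assumed share, SD and power split, and the shift is nil if nobody breathes below 9/min. The primary result is affected only if a spectral index is used as the primary parameter, which the article neither states nor excludes. The conclusion also rests on the physiological assumption that respiratory power follows the breathing rate. It should be corrected because the reading is fixed in the text and the check uses data already recorded.

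**What to change.** Amend section 3.2.1 as follows:
- Keep the fixed bands as the main definition for all recordings in both arms.
- For each analysed recording, derive the mean respiratory rate from the belt, and report it by arm at M1 and M3 beside the heart rate variability results.
- State that LFnu, HFnu and LF/HF will not be interpreted as sympathetic or vagal in recordings below 9/min (0.15 Hz).
- Add a sensitivity analysis of the spectral indices that takes the recorded respiratory rate into account and is applied identically to every recording in both arms. One option is a respiration-centred band of pre-specified width, with the caveat that at slow rates it also captures non-respiratory LF power.
- Do not switch the band only in slow-breathing recordings.

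The cost is a little more signal processing; no new device, visit or participant is needed. The sensitivity result will be less comparable with published fixed-band values and conditions on a post-randomisation variable, so it should be labelled as supportive only. The sample size does not change.

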#### 3.2.2. Skin Conductance

Skin conductance will be measured in micro-Siemens with sampling rates at 2, 4, 8, 16 and 32 Hz during the phases 1 to 3. The skin conductance sensor (Empatica E4, Milano, Italy) is set on a wristband [53]. 

#### 3.2.3. Questionnaires

The REDCap^®^ questionnaires in digital format will be automatically emailed to participants. They will then have to click on a link to answer. Only the short one will be sent to the participants. The long questionnaire will be completed during monthly appointments (M0, M1, M3, M5 and M7).

The short questionnaire will assess sociodemographic such as gender, age and recent stressful event. There are visual analog scales (VAS) too such as stress at home, fatigue, sleep quality, anxiety, mood, family support, stress at work, burnout, job control, job demand, hierarchy support, colleagues support, effort reward imbalance on a horizontal, non-calibrated line of 100 mm, ranging from very low (0) to very high (100) [36,54]. Lifestyle will be assessed in short questionnaire: physical activity, addiction (alcohol, cannabis, and tobacco) and coffee/tea. Sophrology practice will be assessed too: number of sessions per week, stress before and after the last sophrology session.

The long one will contain the following questionnaires. The Recent Physical Activity Questionnaire (RPAQ) [49] is designed to assess the level of physical activity and sedentary behavior in adults over the past four weeks. It is divided into three parts: work and study, home and leisure, and stairs and travel. It classifies individuals into several categories, one based on sedentary time (low; moderate, i.e., 3–7 h/day; or high, i.e., >7 h/day) and one based on physical activity level (<8.3 MET.h/wk: inactive or >8.3 MET.h/wk: active). The Hospital Anxiety and Depression scale (HAD) [55] evaluate the frequency of anxious (HAD-A: 7 items) and depressive (HAD-D: 7 items) symptoms using a 14-items questionnaire. For each item, four frequency choices are offered ranging from “never” to “always”. For the two components (HAD-A and HAD-D), scores make it possible to determine two levels of symptomatology: “possible symptomatology” (from 8 to 11) and “clear and proper diagnosis of depressive or anxiety disorder” (>11). The Maslach Burn-out Inventory (MBI) [40] is designed to assess the three components of the burn-out syndrome: depersonalization (five items), emotional exhaustion (nine items), and reduced personal accomplishment (eight items). It is composed of 22 items related to personal feelings or attitudes. Items are made of a seven frequency choices, varying from “never” to “every day”. A score, which can be split into three categories (low, average, or high) is determine for each components separately but there are not merge to obtain a global score. The Job Demand-Control-Support (JDSC) questionnaire of Karasek [27] is a twenty-six-item questionnaire decomposed into nine items to evaluate job demand, nine items to evaluate job control and eight items to measure social support. The items are made of a four-point scale measuring level of agreement, ranging from “strongly disagree” to “strongly agree”. A reverse scoring is required for 5 of the 26 items. According to French data, the job demands is considered as high for a score higher than 20 and the job control and social support as low for score lower than 71 and 24, respectively. High demand and low control characterize jobstrain. Jobstrain associated with low social support reflects the isostrain situation. We would ask the participants to fulfil the questionnaire from memories that they keep of their work. The Effort-Reward Imbalance Questionnaire (ERI) is a self-administrated test assessing psychological distress and health problems that may occur when there is an imbalance between the efforts required by the work and the rewards received. We used the 23 items of the short version of the ERI model exploring efforts (six items), over commitment (six items), and rewards (eleven items) [43]. Items of ERI were scored on a five-point Likert-type scale, ranging from 1 = disagree to 5 = agree and very disturbed. A ratio extrinsic efforts and rewards can assess the imbalance between these two dimensions. A ratio greater than one defines employees exposed to an imbalance between efforts and rewards [43]. The Twenty-item Toronto Alexithymia Scale (TAS20) [44,45,46,47,48] is the most widely used self-report measure of alexithymia. Alexithymia (from the Greek, a = lack of, lexis = work or word, and thymos = mood or emotion) refers to severe reductions in both the cognitive and affective components of emotional experience. For this scale, a three-factor structure was proposed: difficulty identifying feelings, difficulty describing feelings and externally oriented thinking. Responses are made on a 5-point scale from “strongly agree” to “strongly disagree”. The long questionnaire also contains questions about food intake in the last month.

### 3.3. Data Analysis

The SO-WELL trial statistical analysis plan (and its successive versions) will be kept in the study records. The statistical analysis plan may be revised during the study, e.g., in order to take into account amendments to the protocol or any change in the conduct of the study that may have an impact on the statistical analysis plan as described in its current version.

Statistical analysis will be performed using Stata software (v16, Stata-Corp, College Station, TX, USA). According to the International Conference on Harmonization Good Clinical Practice guidelines, analyses will be conducted before the breaking of the randomization code. The primary analyses will be carried out in two stages. First, using intention-to-treat analysis and applying imputation data method for missing data. Then, using per-protocol analysis which consists of consider only participants without missing data for the primary endpoint. 

Categorical parameters will be described in terms of numbers and frequencies, whereas continuous variables will be expressed as mean and standard deviation or median and (inter-quartile range) according to statistical distribution. The assumption of normality will be studied using Shapiro–Wilk test. 

At inclusion, participants will be characterized and compared between groups according to the following variables: respect with eligibility criteria, epidemiological, clinical and treatment attributes. Using the characteristics of the participants and potential factors associated with the primary outcome, the comparability at baseline between groups will be assessed. According to both clinical and statistical considerations, a possible difference between the two groups on one of these characteristics will be determined. 

Intergroup comparisons will be systematically conducted (i) without adjustment and (ii) by adjusting for factors whose distribution could be unbalanced between groups. 

All statistical tests will be two-sided and *p* < 0.05 will be considered significant. Most of analyses of the secondary evaluation criteria will be exploratory. As discussed by Feise [39], the adjustment of the type I error will not be systematically proposed, but case by case in view of clinical considerations and not only statistical. 

#### 3.3.1. Analyses for the Primary Outcome

To compare the primary endpoint between groups, we will use Student’s t-test, or the non-parametric Mann–Whitney test if assumptions of t-test are not met. 

For the primary analysis, the intention-to-treat analysis will be considered, i.e., the comparisons between groups (“intervention” group and “waiting list” group) between M1 and M3. To prevent attrition bias, imputation of the missing data is planned. Then, the analysis of the primary outcome will be completed by multivariable analysis using a linear mixed model to compare HRV parameters between randomized groups considering (i) covariates identified according to clinical relevance (such as sex, age, number of complete sessions performed, occupational characteristics) and univariate results and (ii) session as random effects (to measure the variability between and within session). We will study the normality of the residuals from linear regression. If needed, a logarithmic transformation of the dependent variable will be suggested. Effect sizes and 95% confidence intervals will be used to express result. 

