### 2.6. Outcomes

The main outcome is heart rate variability change between M1 and M3. HRV will be measured using Zephyr™ BioHarness™ BT (Zephyr Technology, Annapolis, MD, USA). The main secondary outcomes are subjective (questionnaires: perceived stress, personality and perception of work, etc.) and objective markers of stress (biomarkers of stress such as other measures of the activity of the autonomic nervous system, DHEAS, cortisol, etc.). All outcomes are presented in Table 1.

For both groups (interventional and control groups): (i) heart rate variability, skin conductance and saliva biomarkers will be assessed once by week during the intervention period (6 to 8 sophrology sessions) and once by month the rest of the time; (ii) the short questionnaire will be collected once a week during the whole protocol (1–2 min); and (iii) the long questionnaire will be assessed only 5 times: at baseline (M0), month 1 (M1), month 3 (M3), month 5 (M5), and the end of the protocol (M7).

Outcomes will be collected by a research assistant without any link with the randomization process nor the intervention. The independence is necessary to minimize contamination of the intervention group, particularly in study designs which cannot be blinded.

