Allostatic load **	Cortisol	Saliva sampling and deep-freezing	**Intervention**: 1 during each sophrology sessions (6 to 8 sessions) **Rest of the time**: 1 by month		[23,24,25] (1, 2)
	DHEAS	Saliva sampling and deep-freezing			[23,24,26]
	Leptin	Saliva sampling and deep-freezing			[27,28]
	Ghrelin	Saliva sampling and deep-freezing			[28,29,30,31]

* Adjustment variables; ** Saliva samples upon waking up to control the circadian rhythm of biomarkers.

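### The primary test on HRV change ignores baseline HRV and lets the data choose between a mean and a rank comparison; the adjusted analyses select covariates from the data and include a post-randomisation one

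*Protocol article*

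**What the plan says.** - Endpoint (2.6): "The main outcome is heart rate variability change between M1 and M3".
- Primary test (3.3.1): "we will use Student’s t-test, or the non-parametric Mann–Whitney test if assumptions of t-test are not met". On distributional checks, 3.3 says "The assumption of normality will be studied using Shapiro–Wilk test".
- Adjustment in general (3.3): between-group comparisons are run unadjusted and then "by adjusting for factors whose distribution could be unbalanced between groups".
- Completing model (3.3.1): "Then, the analysis of the primary outcome will be completed by multivariable analysis using a linear mixed model". Its covariates are "covariates identified according to clinical relevance (such as sex, age, number of complete sessions performed, occupational characteristics) and univariate results".
- Table 1 (3.2) labels the demographic row "Adjustment variables". That row includes recent stressful events, which are asked at inclusion and then weekly.
- Schedule (2.2 and 2.6): HRV is recorded monthly outside the session period. The intervention group has a one-month control period before its sessions and the deferred group has three months. On this schedule the M0 and M1 readings precede any session in either group.
- Sample size (3.1): effect size about 0.5, two-sided 5%, 90% power, 85 per group, raised to 100 for loss to follow-up.

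**The concern.** Three features of the analysis are poorly fixed.

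1. A t-test on change uses M1 only by subtraction. Regressing M3 on M1 estimates the same treatment difference with smaller variance whenever the two readings are imperfectly correlated. M0 is not used at all.
2. The t-test compares mean changes and Mann–Whitney compares ranks. If the observed distribution decides between them, the article does not fix in advance what the primary result estimates.
3. The adjusted analyses take covariates from observed imbalance and from associations in the trial data, so several adjusted results are possible. One named example, the count of completed sessions, is measured after randomisation and is determined largely by allocation.

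At stake are precision, a clearly defined primary estimate, and adjusted results that can be read as support for it.

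**Working it through.** **The plan's own figure.** With d = 0.5, two-sided 5% and 90% power, n = 2 × [(1.960 + 1.282)/0.5]² = 84.06, so 85 per group. This matches 3.1. An exact noncentral-t calculation gives 86, with 89.99% power at 85. The 100 per group corresponds to 15% loss (100 × 0.85 = 85).

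**Variances, with the SD of one HRV reading set to 1.** Let r be the correlation between readings. The article gives no value, so 0.3 to 0.9 is assumed.
- Change score: 2(1 − r).
- ANCOVA on M1: 1 − r². Ratio to change: (1 + r)/2.
- ANCOVA on M0 and M1, with equal correlations between all readings (compound symmetry): 1 − 2r²/(1 + r). Ratio to change: (1 + 2r)/[2(1 + r)].

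**If 0.5 is in SDs of the change.** Required n is 84.06 × ratio. Power at 85 is Φ(0.5/√ratio × √42.5 − 1.960). On this normal approximation the planned test has 90.3% power.

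| r | Ratio, M1 | n per group | Power at 85 | Ratio, M0 and M1 | n per group | Power at 85 |
|---|---|---|---|---|---|---|
| 0.3 | 0.65 | 55 | 98.1% | 0.615 | 52 | 98.6% |
| 0.5 | 0.75 | 64 | 96.4% | 0.667 | 57 | 97.9% |
| 0.7 | 0.85 | 72 | 94.2% | 0.706 | 60 | 97.3% |
| 0.9 | 0.95 | 80 | 91.7% | 0.737 | 62 | 96.7% |

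**If 0.5 is in SDs of a single reading.** For r = 0.3 / 0.5 / 0.7 / 0.9, the change-score test needs 118 / 85 / 51 / 17 per group and ANCOVA on M1 needs 77 / 64 / 43 / 16. ANCOVA again needs fewer at every r, but at r of 0.7 or more the planned test already has about 99% power or higher.

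**The test switch.** This was simulated with 4,000 runs, 85 per group and r = 0.6, using Mann–Whitney when Shapiro–Wilk rejected in either group.
- Type I error: 4.8% with normal data, 4.7% with log-normal HRV (log-SD 0.5).
- Power, normal data: 89.8%, against 95.6% for ANCOVA.
- Power, log-normal data: 89.4%, against 91.5% for ANCOVA on the raw scale and 95.4% on the log scale.

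**How often the switch could operate.** For change scores at an assumed log-SD of 0.4, r of 0.5 to 0.8 and 85 per group, Shapiro–Wilk rejects in roughly 44 to 49% of arms, and in at least one of the two arms in about 69 to 72% of trials. At log-SD 0.3 the per-arm figure falls to 25 to 26%.

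**The sessions covariate.** Between M1 and M3 the intervention group is offered 6 to 8 sessions and the deferred group none. With group and session count in one model, the group coefficient becomes the contrast for an intervention participant who completed no sessions. The part of the effect delivered through the sessions moves to the other coefficient.

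**The case against.** The strongest defence is that the primary test is not wrong. A t-test on change is unbiased under randomisation, 85 per group reproduces, and power is as stated. This stands. The gain from ANCOVA rests on an unstated correlation and is small with M1 alone when r is high (91.7% at r = 0.9).

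Stronger readings are tempting, but the documents do not support them:
- A reader might infer that the switch inflates false positives. The simulation shows 4.7 to 4.8%.
- A reader might infer that data-driven covariates contaminate the primary test. In 3.3.1 the unadjusted test comes first and the mixed model completes it, so selection affects only the adjusted and completing analyses.
- A reader might infer that normality would almost always be rejected. Rejection of 95 to 96% applies to single log-normal readings at log-SD 0.4, not to the change that is tested. The article also does not make Shapiro–Wilk the mechanical trigger.
- A reader might infer that weekly stressful-event answers enter the primary model. Table 1 only labels the row, and values at inclusion exist too.
- A reader might see the adjustment statements as flatly contradictory. They can be read as a general rule and a model-specific rule.

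The covariate list is open-ended, and details may sit in the unseen SAP. That does not dispose of the point, because the article itself fixes the test, the selection rules and the sessions example.

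One limit remains. The article does not state when randomisation falls relative to M1. M1 is untreated in both groups but may not strictly precede allocation.

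**Conclusion.** The point holds as one of efficiency and pre-specification. It is not an error in the sample size or in type I error control, and the trial is not shown to be undersized. ANCOVA on M1 HRV would cut variance by 35% at r = 0.3 and 5% at r = 0.9; using M0 as well would cut it by 39% to 26%. If 0.5 is in SDs of the change, power at 85 per group rises from 90% to about 92 to 98% with M1, or about 97 to 98.5% with both readings. These figures assume r throughout, and compound symmetry for the two-baseline case.

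Separately, the switch leaves the choice between a mean difference and a rank comparison to the data, and adjusting for sessions completed removes part of the treatment effect. The sessions fault is the clearest of these because it needs no assumption about r. The changes should be made.

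**What to change.** - Make the primary analysis one pre-specified ANCOVA, or the equivalent mixed model, of M3 HRV on randomised group, with M1 and M0 HRV and a short fixed list of baseline covariates: age, sex and occupation.
- Fix the scale in advance for the chosen HRV index. Log suits strictly positive indices; pNN50 can be zero and needs another choice.
- Delete covariate selection by observed imbalance and by univariate results.
- Exclude post-randomisation covariates: sessions completed, and any stressful-event value recorded after baseline.
- Keep the unadjusted t-test and the rank test as sensitivity analyses.
- State when randomisation occurs relative to M1.

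The cost is analysis wording. No new data, visits or participants are needed.
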